## Introduction

Glaucoma is a chronic optic nerve disease involving progressive loss of retinal ganglion cells, necessitating long-term treatment with minimal side effects. Some patients may choose to supplement their conventional medical interventions with complementary or alternative medicine [1-3].

In complementary and alternative therapies, there is literature on treating glaucoma with acupuncture, auricular acupressure [4], herbal medicine [5,6], nutritional supplements [7], and Ayurvedic medicine [8]. Possible mechanisms for acupuncture treatment have been proposed, including the release of neurochemical substances through acupuncture stimulation; the influence of acupuncture on ocular blood flow parameters [9,10]; and the upregulation of neurotrophic factors, such as nerve growth factor and brain-derived neurotrophic factor expression in the retina [11]. In an observation study on acupuncture treatment for glaucoma, Law et al [12] conducted a prospective study including 11 patients with glaucoma and observed a short-term increase in intraocular pressure (IOP) after acupuncture [12]. However, another study presented a different perspective, suggesting that acupuncture at the acupoints Jingming (BL1) and Qiuhou (EX-HN7) was beneficial in reducing IOP [13]. Systematic literature reviews have also supported the potential of acupuncture in lowering IOP and improving visual fields [14].

The objective of this single-center randomized control trial is to evaluate the clinical efficacy of acupuncture in the context of glaucoma and provide a reference for future clinical treatment guidelines.

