## Methods

### Design and Setting

The study is designed as a single-center, parallel-arm, randomized controlled trial. It will take place in the clinic of China Medical University Hospital. The trial will be conducted from June 2023 until 50 patients finish acupuncture treatment and follow-up assessment. This protocol is reported following the SPIRIT (Standard Protocol Items: Recommendations for Intervention Trials) 2013 statement, which defines standard protocol items for clinical trials [15].

The main purpose of the trial is to investigate the effectiveness of acupuncture in the treatment of glaucoma, including its potential to decrease IOP and reduce optic nerve damage. All participants will be randomly assigned to 2 groups: the treatment group and the control group. Participants in the treatment group will receive acupuncture treatment targeting acupuncture points related to ophthalmology, while participants in the control group will receive minimum acupuncture targeting nonophthalmic acupuncture points.

In addition, all participants will undergo ophthalmic examinations and follow-up. Figure 1 illustrates the enrollment process of the trial. The assessments will include measurements of IOP, heart rate (HR), blood pressure (BP), best-corrected visual acuity (BCVA), central corneal thickness, visual field (VF), optical coherence tomography (OCT) imaging, optical coherence tomography angiography (OCTA), and visual function questionnaire.

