### Outcome Measures

The primary outcome is the change in IOP as measured using the CT-80 Computerized Tonometer (TOPCON). Before the start of the trial, the participants’ baseline IOP will be measured. Subsequently, IOP data will be collected before each acupuncture treatment and 15 minutes after the treatment. By comparing these measurements, the effect of acupuncture treatment on IOP can be assessed.

The secondary outcomes include the long-term effects of acupuncture on the eyes. Baseline measurements and measurements after the completion of the sixth acupuncture session will be taken using OCTA (AngioVue, QuickVue version, Optovue Inc) to assess the vessel density of the radial peripapillary capillary and macula. In addition, VF, OCT, BCVA, central corneal thickness, and 2 questionnaires will be recorded at baseline and during follow-up at week 12. VF measurements will be conducted using the Humphrey Field Analyzer 3 (ZEISS) to measure the mean deviation, pattern SD, and VF index values. OCT imaging will be performed using the ZEISS HD-OCT model 5000, and measurements of the retinal nerve fiber layer, ganglion cell complex and symmetry, and the cup-to-disc ratio will be recorded. The 2 questionnaires used in the trial are the Glaucoma Symptom Scale (GSS; score range 0-100) and the Glaucoma Quality of Life-15 (GQL-15; score range 0-75) [17,18]. These questionnaires are used to quantify the extent of functional impairment or inconvenience in patients with glaucoma. In addition, to ensure the safety of participants during the trial and to address other relevant considerations related to the pathophysiology of glaucoma, BP and HR measurements will be taken at baseline, before and after acupuncture sessions, and during follow-up assessments. Table 1 depicts the trial schedule, illustrating the journey of patients from initiation to the completion of the trial.

**Table 1 table1:** Trial schedule, showing the journey of patients from initiation to the completion of the trial.

Time point		Enrollment	Treatment		Follow-up
		Visit day 1	Week 1-6	Week 6 (after acupuncture)	Week 12
**Eligibility screen**		✓			
**Informed consent**		✓			
**Allocation**		✓			

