### Statistical Analysis

The statistical analysis will be performed by a statistician from the [name]’s laboratory who is completely blind to patient allocation, using SPSS software (version 29.0; IBM Corp). The demographic data between the 2 groups, including sex, age, initial IOP, HR and BP, and BCVA will be compared using the 1-tailed Student *t* test. For the data from the 2 glaucoma questionnaires, a 1-way ANOVA will be used. In addition, a repeated measures analysis will be conducted in the trial. The data will be presented as mean (SD), and a *P* value of less than .05 will be considered statistically significant. Subgroup analysis will be conducted based on factors, such as age; gender; changes in IOP before and after treatment; VF, OCT, and OCTA data; and central corneal thickness, among others. In cases of small sample size, the Mann-Whitney *U* test and the Wilcoxon signed-rank test will be used if data do not follow normal distribution. Missing data will be analyzed using pairwise deletion.

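### Baseline variables, sex among them, are tested with a 1-tailed t test that has no stated direction, and the questionnaire ANOVA does not say which score it uses or whether baseline enters

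*Protocol article*

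**What the plan says.** All statements on tests come from the Statistical Analysis section of the protocol article.

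- **Baseline comparison.** The demographic data, "including sex, age, initial IOP, HR and BP, and BCVA will be compared using the 1-tailed Student" t test. No direction is given, and the section names no test for a categorical variable.
- **Questionnaires.** "For the data from the 2 glaucoma questionnaires, a 1-way ANOVA will be used". The response variable is not stated, and neither is a baseline covariate or a within-person factor.
- **Repeated measures.** "In addition, a repeated measures analysis will be conducted in the trial". No outcome, factor or model is attached to it.

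On the data these tests would meet, the Outcome Measures section says that "2 questionnaires will be recorded at baseline and during follow-up at week 12", and Table 1 agrees: GSS and GQL-15 are ticked at visit day 1 and at week 12. The Design and Setting section fixes two arms: "All participants will be randomly assigned to 2 groups: the treatment group and the control group". Each questionnaire therefore yields two scores per person in two groups.

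**The concern.** **Baseline tests.** A one-tailed test is defensible only where a direction is fixed in advance and the other direction is of no interest. Neither holds for baseline variables in a randomised trial. The test stays silent about imbalance in the untested direction, and in the tested direction it is a two-sided test at .10. Sex is also listed under a t test, which is not the natural test for a proportion.

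**Questionnaires.** With two groups and two visits, a one-factor ANOVA can be set up in several ways. The text does not say which is meant, and the options differ in quality. Some are valid but give up precision, which a trial of this size can ill afford; the article's Conclusions concede that the sample is modest. Others treat two scores from one person as if they came from two people. The baseline score is collected in any case, so not using it well gains nothing.

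**Working it through.** The article gives no figure for either comparison, so there is none of its own to reproduce here. It supplies the design inputs; the rest is assumed.

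**Inputs**
- 20 evaluable per group, alpha .05, effect size 0.40: Sample Size Calculation and Power section. The metric of the 0.40 is not stated, and it is not tied to the questionnaires.
- Two scores per person (baseline, week 12) and two groups: Outcome Measures, Table 1, Design and Setting.
- Correlation rho between baseline and week-12 score: assumed, 0.5 and 0.7 (up to 0.8 in the simulations).
- Standardised difference d: assumed. If the 0.40 is a standardised mean difference, d = 0.40. If it is Cohen's f, then with two equal groups d = 2f = 0.80.

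**1. What the 1-way ANOVA could mean.** Rejection rates under no treatment effect, from simulation with 20 per group and 8,000 runs per setting, rho 0.5 to 0.8:

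| Data entered | Null rejection at .05 | Reading |
|---|---|---|
| Week-12 scores by group | about 0.05 | valid, baseline discarded |
| Change scores by group | about 0.05 | valid, pairing respected |
| Both visits pooled, by group | 0.11 to 0.15 | too liberal |
| Baseline v week 12 within one arm, as independent | 0.0001 to 0.008 | far too conservative |
| Four group-by-visit cells, with a common time shift of 0.8 SD | 0.91 to 0.96 | picks up time, not treatment |

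Only the last three rows, which enter both visits as independent observations, misstate the error.

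**2. Variance of the group difference.** Take equal variances at the two visits and set week-12-only = 1.
- Change score: 2(1 − rho). At 0.5: 2 × 0.5 = 1.00. At 0.7: 2 × 0.3 = 0.60.
- ANCOVA: 1 − rho². At 0.5: 1 − 0.25 = 0.75. At 0.7: 1 − 0.49 = 0.51.
- ANCOVA against change score: (1 − rho²) / [2(1 − rho)] = (1 + rho)/2. At 0.5: 0.75. At 0.7: 0.85.

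**3. Power, two-sided .05, 20 per group.** The noncentrality is d × √(n/2) / √(variance ratio), with √(20/2) = 3.162.
- d = 0.80, week-12 only: 0.80 × 3.162 = 2.53, power 69%.
- d = 0.80, ANCOVA: 2.53/√0.75 = 2.92, power 81%; 2.53/√0.51 = 3.54, power 93%.
- d = 0.40, week-12 only: 0.40 × 3.162 = 1.26, power 23%.
- d = 0.40, ANCOVA: 1.26/√0.75 = 1.46, power 30%; 1.26/√0.51 = 1.77, power 41%.

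At d = 0.80 the simulation agrees: 0.70 for week-12 only, 0.81 and 0.92 for ANCOVA.

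**4. The single tail on sex.** Illustration with 25 per arm, 18 against 11 of one sex:
- 1-tailed t: p = 0.023 in one direction, 0.977 in the other.
- Two-sided t: 0.046. Chi-square without continuity correction: 0.045. Fisher: 0.085.

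The same imbalance passes unnoticed or is called significant according to a direction that the article does not state. The t test as such changes little here, since its two-sided result is almost the chi-square result. The single tail does the damage.

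**The case against.** The strongest reply concerns the ANOVA. An article may leave the response variable to the full protocol or SAP, and a 1-way ANOVA by group on change from baseline would both use baseline and respect the pairing. The section also announces a repeated measures analysis and, for non-normal data in small samples, the Wilcoxon signed-rank test, so within-person pairing was plainly in view. Most of this stands. A reader might infer that the named ANOVA necessarily ignores baseline or pairing and so yields wrong standard errors. The text does not support that: wrong errors arise only if both visits are entered as independent observations, which the article nowhere says. It remains true that neither the repeated measures analysis nor the signed-rank test is assigned to the questionnaires, and that every valid reading of the ANOVA is generally less precise than ANCOVA.

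On the baseline tests, it is fair to say that they feed no treatment estimate and that the mean (SD) will show imbalance in continuous variables whatever the P value. This lowers the stakes but does not justify the single tail. A reader might also argue from the Introduction, which cites a rise in IOP after acupuncture, that a one-directional test is ruled out. That study concerns response to treatment and says nothing about the direction of baseline imbalance. The absence of any stated direction is enough.

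Finally, a reader might extend the criticism to the follow-up analyses of BCVA, VF, OCT and OCTA. The article names no specific test for those, and that may be settled elsewhere.

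**Conclusion.** The point holds in two parts of unequal strength.

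The 1-tailed baseline test is wrong as written: no direction is stated, none would be sensible, and a binary variable is on the list. Its consequences are small, because these are descriptions of the sample.

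The questionnaire ANOVA is under-specified rather than shown to be invalid. On its valid readings the cost is precision. Against week-12 scores alone, ANCOVA would cut the variance by 25% (rho 0.5) or 49% (rho 0.7); against change scores, by 25% or 15%. The gain in power over week-12 scores is about 12 or 24 percentage points if d = 0.80, and about 7 or 18 if d = 0.40. These figures rest on assumed correlations, on two assumed values of d and on 20 evaluable per group. Because GSS and GQL-15 are secondary outcomes and a week-12 comparison is unbiased under randomisation, the severity is minor to moderate.

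**What to change.** 1. For GSS and GQL-15, replace the 1-way ANOVA with a two-sided ANCOVA: week-12 score on group, with the baseline score as covariate, reporting the adjusted difference with its 95% CI. If a 1-way ANOVA is kept, state the response and make clear that each participant contributes one value.
2. Say which outcomes the repeated measures analysis serves.
3. Present baseline variables by group as mean (SD) or n (%) without tests. If tests are kept, use two-sided t tests for the continuous variables and chi-square or Fisher for sex, and delete the 1-tailed wording.

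The cost is a few sentences of analysis text. The baseline scores are already scheduled and the named SPSS software runs these analyses, so no extra visit, measurement or participant is needed.

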**Methods:**

In this single-center randomized controlled trial, participants (N=50) with primary open-angle glaucoma will be randomly assigned to the treatment group, receiving ophthalmic acupuncture with “De Qi” sensation, or the control group, receiving minimum acupuncture stimulation on nonophthalmic acupoints. The intervention will consist of weekly acupuncture treatments for a total of 6 sessions. Participants will be assessed at 8 time points, which are baseline, during the intervention (6 times), and at a 3-month follow-up. The primary outcome measure is a change in the intraocular pressure before and after each acupuncture treatment. Secondary outcomes will include measurements of heart rate and blood pressure before and after acupuncture, best-corrected visual acuity, visual field, optical coherence tomography, optical coherence tomography angiography, the Glaucoma Symptom Scale, and the Glaucoma Quality of Life-15 questionnaire.

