### Sample Size Calculation and Power

Assuming an effect size of 0.40 and a type I error (α) of .05, a sample size of 40 people (20 in each group) is required to achieve a statistical power of 95% CI. Assuming a dropout rate of 25%, a total of 50 people (25 in each group) is needed (Textbox 1).

Inclusion and exclusion criteria.

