### Randomization and Allocation Concealment

The participants will be randomly assigned to 2 groups with a 1:1 ratio using random number generation in Microsoft Excel. A computer-based simple random sampling method without stratification with a 1:1 ratio will be used. After the random allocation is completed, the researchers will assign sequential numbers (1-50) to the participants and prepare 50 folders. The appearance of the folders will be identical for both groups, and the section containing the participant’s group and the intervention measures will be sealed. When participants complete the informed consent process, the acupuncturist will unseal the section and begin the acupuncture treatment.

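### Subgroups are to be formed by the change in IOP, which is the primary outcome and is seen only after randomization; baseline IOP should take its place

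*Protocol article*

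**What the plan says.** The subgroup sentence in the Statistical Analysis section reads: "Subgroup analysis will be conducted based on factors, such as age; gender; changes in IOP before and after treatment". It goes on to name VF, OCT and OCTA data and central corneal thickness, and leaves the list open.

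The abstract defines the primary endpoint: "The primary outcome measure is a change in the intraocular pressure before and after each acupuncture treatment". Outcome Measures repeats it ("The primary outcome is the change in IOP as measured using the CT-80 Computerized Tonometer (TOPCON") and gives the timing: "IOP data will be collected before each acupuncture treatment and 15 minutes after the treatment".

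Allocation is 1:1 and simple: "A computer-based simple random sampling method without stratification with a 1:1 ratio will be used". Design and Setting states what acupuncture is expected to do, "including its potential to decrease IOP and reduce optic nerve damage".

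**The concern.** A subgroup comparison keeps the protection of randomization only if the factor that defines the subgroup cannot be affected by treatment. Age and gender meet that condition. The change in IOP over treatment does not, because it is the quantity that acupuncture is meant to move.

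If acupuncture works, some treated patients show a large IOP fall only because they were treated, while a control patient with the same fall reached it through other characteristics. Patients who share a level of IOP change therefore differ systematically between arms. Two consequences follow:

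- Part of the real IOP effect disappears inside each subgroup.
- Outcomes that treatment does not affect can differ between arms inside each subgroup.

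The article offers the trial as a reference for future treatment guidelines, and findings by degree of IOP response could be read in that light.

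**Working it through.** **Is the factor the primary outcome?** The subgroup sentence names the changes in IOP before and after treatment. The abstract's primary outcome is the change in IOP before and after each treatment. The two describe the same quantity. It cannot be read as baseline IOP: the same Statistical Analysis section calls the baseline value the initial IOP when it lists the characteristics to be compared between groups, so the authors had a separate term for it.

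**Size of the distortion.** The plan states no figure here, so there is none to reproduce. The calculation below is an illustration.

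*Inputs from the document:* 1:1 allocation and 25 patients per arm ("Assuming a dropout rate of 25%, a total of 50 people (25 in each group) is needed"). The effect size of 0.40 ("Assuming an effect size of 0.40 and a type I error (α) of .05") is used only for scale, because its type is not stated. Read as a standardized mean difference, it gives d = 0.40. Read as Cohen's f with two equal groups, it gives d = 2 × 0.40 = 0.80. Both are shown.

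*Assumptions:* normally distributed IOP change in SD units, with mean −d in the treated arm and 0 in the control arm; a split at the pooled median; and a second outcome with no treatment effect whose within-arm correlation with IOP change is r = 0.25 or 0.5.

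*Formulas:* By symmetry the pooled median is −d/2. Write p = Φ(d/2) and φ = the standard normal density at d/2. In the half with the larger IOP fall:

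- share of the treated arm = p; share of the control arm = 1 − p
- selection term g = φ/(1 − p) − φ/p
- arm difference in IOP change (treated minus control) = −d + g
- arm difference in the unaffected outcome = r × g

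The other half gives the same two differences.

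*d = 0.40:* p = 0.579, φ = 0.391.
- Patients: 25 × 0.579 = 14.5 treated and 25 × 0.421 = 10.5 control.
- g = 0.929 − 0.675 = 0.254.
- IOP difference: −0.40 + 0.254 = −0.146.
- False difference: 0.25 × 0.254 = 0.064 and 0.5 × 0.254 = 0.127.

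*d = 0.80:* p = 0.655, φ = 0.368.
- Patients: 25 × 0.655 = 16.4 treated and 25 × 0.345 = 8.6 control.
- g = 1.069 − 0.562 = 0.507.
- IOP difference: −0.80 + 0.507 = −0.293.
- False difference: 0.25 × 0.507 = 0.127 and 0.5 × 0.507 = 0.253.

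*d = 0:* p = 0.5, so g = 0 and there is no distortion.

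| True IOP effect (SD) | IOP effect seen in each half | False difference, r = 0.25 | False difference, r = 0.5 |
|---|---|---|---|
| 0 | 0 | 0 | 0 |
| 0.40 | 0.15 | 0.06 | 0.13 |
| 0.80 | 0.29 | 0.13 | 0.25 |

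Simulation gives the same results to within sampling error: 0.14 and 0.29 SD for the IOP difference.

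**Direction.** The false difference, +r × g, has the opposite sign to the IOP effect. If a larger IOP fall goes with a better outcome, treated patients inside each half look worse than controls.

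**Against the noise.** At d = 0.40 the standard error of an arm difference in one half is about √(1/14.5 + 1/10.5) ≈ 0.40 SD. A bias of 0.13 SD then raises the two-sided false-positive rate from 5% to about 6%. At d = 0.80 and r = 0.5 it is about 9%.

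**The case against.** **The sentence may be loose drafting.** The list mixes patient characteristics with trial measurements, ends openly, and gives no cut-point, no responder category and no statement that arms will be compared within levels of IOP change. It might have been meant partly as a list of endpoints to examine within subgroups, and fuller definitions may sit in a document that is not shown. That is possible. But the sentence bases the subgroups on these factors and puts IOP change next to age and gender. The point concerns what the article states, and if something else was meant the sentence still needs correcting. What stands of the objection is that the median split is an assumption.

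**VF, OCT and OCTA.** A reader might infer that these entries share the fault because they are secondary outcomes. The document does not support that. Table 1 schedules all of them, and central corneal thickness, at enrollment as well, and the wording about change attaches to IOP alone. Taken at baseline they are legitimate factors; they only need to be called baseline.

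**A false benefit in responders.** A reader might also infer that selection alone could yield a claim that acupuncture helps the visual field in patients whose IOP fell. Under the natural assumption that a larger IOP fall goes with a better field, the artefact runs the other way. It would favour acupuncture only if a larger fall went with a worse field, which nothing in the document suggests.

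**Size.** The false difference depends on assumed correlations and is small beside the sampling error at 25 per arm. That stands and limits the severity. The shrinkage of the IOP effect does not depend on those correlations, although nothing says that IOP would be re-tested inside these subgroups.

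**Conclusion.** The point holds for the IOP-change entry alone. As written, the plan forms subgroups on its primary outcome, and comparisons of arms within them are not randomized if acupuncture changes IOP. The figures in the table rest on normality, a median split, the effect sizes of 0.40 and 0.80 SD and the assumed correlations, so they show the order of magnitude and do not predict this trial's results. The distortion is absent if treatment leaves IOP unchanged; it arises when the trial's hypothesis is true.

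Severity: should be fixed. A reader might infer that the trial's main result is compromised. It is not: the randomized comparison of the primary outcome, the sample size and the data collection are untouched by one entry in a secondary subgroup list.

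**What to change.** In the subgroup sentence of the Statistical Analysis section:

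1. Replace the entry on changes in IOP with baseline IOP.
2. State that VF, OCT, OCTA and central corneal thickness subgroups use the enrollment values already scheduled in Table 1.
3. State that subgroups are tested as group-by-factor interactions.
4. If the link between IOP change and VF or OCT is of interest, report it as a descriptive association within each arm, not as a subgroup treatment effect.

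The cost is about one sentence of wording, with no further patients, visits or measurements. The change should be made before the data are analysed.

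### Subgroup factors form an open list, not tied to baseline values, under the general P<.05 rule

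*Protocol article*

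**What the plan says.** All the relevant analysis text is in the Statistical Analysis section of the protocol article. It sets one threshold, under which a P "value of less than .05 will be considered statistically significant", and makes no exception for any type of analysis. The next sentence reads: "Subgroup analysis will be conducted based on factors, such as age; gender; changes in IOP before and after treatment", then adds visual field, OCT and OCTA data, and closes with "and central corneal thickness, among others". The outcome to be examined by subgroup is not named.

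Outcome Measures and Table 1 give the timing of the listed measurements. Visual field, OCT and central corneal thickness are taken at enrolment and at week 12. OCTA is taken at enrolment and after the sixth session.

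Sample Size Calculation and Power states that "a sample size of 40 people (20 in each group) is required", and raises this to 50 for dropout.

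**The concern.** Two features of the sentence are at fault as written.

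First, the list is open at both ends. Any factor added after the data have been seen would still be consistent with the published protocol, so the public record could not separate a planned subgroup from a later one. Under the general threshold, a result from such a subgroup could be called significant.

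Second, four of the named factors also exist as values taken after treatment begins, and the sentence does not say which values define the subgroup. A subgroup formed on a week 6 or week 12 value may itself be shaped by treatment, and a comparison of arms within it no longer rests on randomisation.

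At stake is how the trial would be read. The article says that it should inform future treatment guidelines. A trial with no overall effect could be reported as showing benefit in, say, older patients or those with thin corneas.

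**Working it through.** **Inputs from the article.** 20 evaluable patients per arm; threshold .05; seven list entries (age, gender, IOP change, visual field, OCT, OCTA, central corneal thickness). IOP change is the primary outcome itself, which is a separate problem, so it is left out of the main count. That leaves six factors. Only age and gender are unambiguously baseline factors.

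**Assumptions, because the article does not give them.** One outcome, normally distributed; no true effect in anyone; each factor an independent split of the 40 patients into 20 and 20; two-sided tests. The article does not say whether arms would be compared within each level or by an interaction test, so both are shown.

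**Interaction tests.** One test per factor, close to independent, so the chance of at least one P<.05 is 1 − 0.95^k:
- k = 2: 1 − 0.9025 = 9.8%
- k = 3: 1 − 0.8574 = 14.3%
- k = 6: 1 − 0.7351 = 26.5%

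**Within-level tests.** Each factor gives two t tests, but different factors reuse the same patients, so 1 − 0.95^(2k) is too high (46.0% for six factors). Simulation is needed.

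| Factors | Within-level, 20 per arm | Within-level, 200 per arm | Interaction, 20 per arm (simulated) |
|---|---|---|---|
| 2 | 17.2% | 15.4% | 9.7% |
| 3 | 22.4% | 20.8% | 14.0% |
| 6 | 33.8% | 32.3% | 26.5% |

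The 20-per-arm columns use 20,000 null trials and the 200-per-arm column 6,000. Separate runs of 5,000 and 10,000 trials gave 33.3% and 33.6% for six factors within level. A tenfold larger trial barely changes the rate, so the number of tests sets it.

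**Sensitivity.** With all seven entries, and correlation between the factors' underlying values from 0 to 0.5, the chance is 35–38% for within-level tests and 26–31% for interaction tests. It passes one half only at about 14 independent tests (1 − 0.95^14 = 51.2%).

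**What the small sample does.** A two-level split leaves about 10 per arm per level. Let d be the standardised difference between arms. The sample-size section's effect size of 0.40 does not say whether it is d or Cohen's f, so both readings are shown; f = 0.40 corresponds to d = 0.8 with two groups.
- Power of a two-sided t test, 10 versus 10: about 13% at d = 0.4 and 39% at d = 0.8.
- Power of an interaction test: the standard error of the difference between two subgroup effects is √(4/10) = 0.632 SD. Power is about 9% if the effects differ by 0.4 SD and 24% if they differ by 0.8 SD.
- Smallest observed difference that reaches P = .05, 10 versus 10: 2.101 × √(2/10) = 0.94 SD. A true effect of 0.4 SD can be significant only if it is overestimated at least 0.94/0.4 = 2.3 times.

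**The case against.** The strongest reply is that this is a condensed article. An interaction test, a multiplicity rule and an exploratory label are details that commonly sit in a statistical analysis plan, and none is shown here. That stands: their absence is not counted as a fault. What remains is what the article does state, namely an open list, factors not tied to baseline and one threshold without exception.

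A second reply is that the statistician is blind to allocation, which limits the choice of factors by their treatment effect. This is a real but partial safeguard, because it neither closes the list nor ties it to baseline.

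A third is that the sentence may mix subgroup factors with measures to be analysed, so that only age and gender are clearly factors. That reading gives the two-factor figures, 17% or 10%. The ambiguity is itself a reason to rewrite the sentence.

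A fourth is that a null trial rescued by a subgroup presupposes a non-significant overall result. Conditioning on that lowers the within-level range to roughly 13% for two factors and 31% for six, a modest change. It is also fair that IOP change is the single named primary outcome, and that no part of the article says a subgroup result would support an efficacy claim.

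**Conclusion.** The point holds as a defect of wording. The plan as written would allow chance subgroup effects, some possibly in subgroups defined after treatment began, to be called significant. On one outcome with no true effect, the chance of at least one is about 17%, 22% and 33–34% for two, three and six factors tested within levels, or about 10%, 14% and 27% with interaction tests. These figures rest on independent two-level splits and two-sided tests, which the article does not specify. Additional outcomes or factors would raise them. The primary comparison is not affected.

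Three stronger conclusions that a reader might draw are not supported:
- That a false subgroup finding is likely. For the named factors on one outcome the risk is well below even odds.
- That 20 patients per arm causes the false positives. The rate is nearly the same at 200 per arm; the small sample instead makes any significant subgroup less credible and its size inflated.
- That the plan breaks a promise of 5% error across subgroups. The article gives a type I error for the sample size and a threshold for individual P values, and claims no familywise control over subgroups.

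**What to change.** In the Statistical Analysis section:
- Delete the closing words that leave the list open, and the wording that makes the named factors mere examples.
- Name a few factors, all measured at baseline, for example age, sex and baseline central corneal thickness.
- Assess each by one treatment-by-factor interaction estimate with a 95% CI, on the primary IOP outcome only.
- State that subgroup results are exploratory and exempt from the P<.05 significance rule.

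This is a change of text and needs no extra patients, visits or measurements. The cost is that subgroup results can then only generate hypotheses. At about 10 patients per arm per level, they could do little more than that in any case.
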